## Abstract

**Introduction::**

Knee osteoarthritis is a common condition that affects daily functioning and decreases the quality of life. There are many ways of treatment depending on the stage of the disease. Advanced cases are qualified for arthroplasty, which is an extensive and demanding surgical procedure. Less advanced stages are treated in various ways: from rehabilitation, through oral and intra-articular pharmacotherapy, to surgical treatment (arthroscopy, osteotomy). Because surgical treatment is risky, scientists focus on less invasive therapeutic methods. The most valuable management is based on regeneration. Mesenchymal stromal cells (MSC) derived from the adipose tissue have a great regenerative and anti-inflammatory potential, therefore an attempt is being made to take advantage of them in knee osteoarthritis treatment.

The study aims to compare the clinical effects of treatment of knee osteoarthritis using adipose tissue MSC obtained by an enzymatic method with the outcomes of the therapy with the mechanically fragmented adipose tissue.

**Methods::**

One hundred adults with primary knee osteoarthritis will undergo lipoaspiration under sterile conditions. The collected lipoaspirates will be further processed, depending on the randomly assigned group-enzymatically with the use of collagenase or mechanically using the Lipogems system. The preparations will be administered to the patients’ knee joints in the operating room under ultrasound control.

The results of treatment will be assessed using Knee Injury and Osteoarthritis Outcome Score, measuring the flexibility of the knee joint, evaluating joint gap in X-ray and the quality of cartilage in magnetic resonance T2-mapping during 1 year after treatment.

**Discussion/conclusion::**

Identification and functional analysis of the regenerative capacity of adipose-derived MSC depending on three variables (body weight, sex, and age) will help to develop a targeted therapy for different groups of patients and will determine the effectiveness of both methods of treatment. An attempt will be made to identify groups of patients with the greatest regenerative potential of the adipose tissue, and thus indicate those with the most probable improvement of the joint condition.

**Trial registration::**

This study protocol has been approved by the Ethics Committee of Medical University of Warsaw and registered on www.clinicaltrials.gov: NCT04675359 (06 Jan 2021)

## Introduction

1

Knee osteoarthritis is one of the basic diseases in orthopedics. It impairs the function of the joints in about 10% of people over 55 years of age; in 25% the condition causes severe disability.^[1]^ The disease cannot be cured, but only slowed down. Joint pain and stiffness effectively hinder daily functioning. Cases of advanced osteoarthritis are qualified for arthroplasty, which is an effective but permanently mutilating procedure, and therefore it is considered a last resort. Less advanced stages of the disease are treated in various ways: from rehabilitation, through oral and intra-articular pharmacotherapy, to surgical treatment (arthroscopy, osteotomy). Because surgical treatment is burdensome and risky, it is worth focusing on less invasive therapeutic methods. The most valuable management is based on tissue regeneration. Following the trend in osteoarthritis research, regenerative medicine seems to be the treatment of the future.

The adipose tissue is considered the best source of mesenchymal stem cells (MSC) – there are many more MSC than in the bone marrow,^[2]^ they are easy to collect by lipoaspiration (colloquially liposuction). MSC are multipotent cells having mainly anti-inflammatory, immunomodulating, and trophic activity.^[3]^ The attempts are made to use the cells in various fields of medicine. Most of the research has been carried out in vitro and on animals. Scientists have been interested in the topic for over 20 years; in the last few years, the first preliminary reports on using human adipose-derived mesenchymal stromal cells (AD-MSC) appeared. For instance, the administration of the cells to the joints together with platelet-rich plasma is applied to reduce pain.^[4]^ A similar experiment was based on injecting AD-MSC of different densities to arthritic joints. The results of the self-assessment questionnaire revealed a reduction in pain and improvement of the joint function, as well as a decrease of the size of cartilage defects and increase the volume of cartilage in arthroscopic images, while the histological examination showed hyaline-like cartilage regeneration in patients who received the highest dose of cells.^[5]^ No side effects were reported. Another attempt to use these cells in humans applies to meniscal tears. A case of a healed meniscus tear in an adult was published with a significant decrease of pain after the AD-MSC injection in the knee joint.^[6]^ There were also satisfying results of the use of AD-MSC in the first carpometacarpal joint with osteoarthritis. Significant decrease of pain and improvement of hand function were achieved.^[7]^

Despite the growing interest in MSC, the knowledge about them still needs to be completed. More scientific studies, both laboratory and on humans, are necessary to explore the subject. Great potential of AD-MSC proven in vitro requires a clinical application. Cell therapies might be the answer to current problems in many diseases, including osteoarthritis, which leads to disability by a gradual deterioration in everyday functioning. Nowadays there are two major ways of processing adipose tissue available: enzymatic digestion to obtain stomal-vascular fraction (SVF) rich in MSC and mechanical fragmentation, rinsing and clarification of the tissue to create a product easy to inject, which is less purified but much easier to implement.

## Materials and methods

2

### Study design

2.1

The study will be carried out in the Orthopedics and Rehabilitation Clinic of Medical University of Warsaw. Based on the calculation of the sample size using power analysis of the test, investigators plan to include 100 adults with primary knee osteoarthritis in this study. The patients will undergo lipoaspiration under sterile conditions of the operating theatre, the collected lipoaspirates will be further processed depending on the randomly assigned group:

enzymatically with the use of collagenase, ormechanically using the Lipogems system.

After collection, lipoaspirates will be immediately transferred to the laboratory of the Department of Regenerative Medicine with a tissue and cells bank in Warsaw, and the preparations will be administered to the patients’ knee joints in the operating room under ultrasound control.

### Inclusion/exclusion criteria

2.2

Inclusion criteria:

Adults with symptomatic gonarthrosis diagnosed based on the X-ray, MRI, and clinical examination, previously unsuccessfully treated (rehabilitation, NSAIDs, hyaluronic acid, and platelet-rich plasma).Primary knee osteoarthritis.Willingness and consent to participate in the study.Readiness to attend control visits.

Exclusion criteria:

Failure to meet the inclusion criteria.Active chronic infection.Metal implant made of a ferromagnetic material that will exclude the patient from magnetic resonance imaging.Use of anticoagulants.General and intra-articular use of steroids during the last year.Pregnancy and breastfeeding.Any autoimmune and rheumatic disease, or conditions that influence the accuracy of test results.Taking drugs or cytostatic medications in the last 30 days.Mental disorders, alcohol, and drug addiction.

### Interventions

2.3

The aim of the study is to compare the clinical effects of treatment of knee osteoarthritis using adipose tissue MSC obtained by an enzymatic method (collagenase digestion) with the outcomes of the therapy with the mechanically fragmented adipose tissue (using Lipogems system).

Lipogems system is defined as a minimal tissue manipulation system. It is a sterile single-use medical device intended for the closed-loop processing and transferring of autologous adipose tissue in a single surgical step.

In contrast, the administration of preparations produced using a collagenase digestion requires advanced actions in the laboratory of the tissue and cells bank, in which the specimens of SFV are prepared.

Both interventions demand adipose tissue collecting. Lipoaspiration will be performed using blind cannulas and vacuum syringes introduced through the abdominal wall with a 3-mm incision on the skin after previous injection to the adipose tissue with modified Klein's solution (500 ml of saline solution, 1 ml of adrenaline, and 40 ml of 2% lignocaine), which makes the collection easier. 10 ml of the collected adipose tissue will be used to examine the samples after previous gradient drainage from Klein's solution. Immediately after collection, the samples will be sent to the laboratory for analysis (cell count testing, culture, phenotype identification, and analysis by flow cytometry).

### Outcome measurements

2.4

The patients will be monitored in the hospital outpatient clinic for 1 year after the procedure; the control visits will take place: after1, 3, and 6 months and after a year. A physical examination and the assessment using the Knee Injury and Osteoarthritis Outcome Score (KOOS) will be performed. Before the procedure and after 1 year, an X-ray and MRI with T-2 mapping will be carried out to evaluate the condition of the cartilage.

Primary outcome measures:

Changes in patients reported outcome measures –KOOS

The KOOS is self-administered and assesses five outcomes: pain, symptoms, activities of daily living, sport and recreation function, and knee-related quality of life. The KOOS's five patient-relevant dimensions are scored separately: pain (nine items); symptoms (seven items); ADL function (17 items); sport and recreation function (five items); quality of life (four items). A Likert scale is used and all items have five possible answer options scored from 0 (no problems) to 4 (extreme problems) and each of the five scores is calculated as the sum of the items included.

Scores are transformed to a 0-100 scale, with zero representing extreme knee problems and 100 representing no knee problems as common in orthopaedic scales and generic measures. Scores between 0 and 100 represent the percentage of total possible score achieved.

[Time frame: 1, 3, 6, and 12 months after procedure]

Changes in the flexibility of the knee joint

Range of motion assessment by goniometer measurements

[Time frame: 1, 3, 6, and 12 months after procedure]

Secondary outcome measures:

Changes in X-ray imaging of the knee joint in a standing position (AP view)Articular cartilage volume evaluation by joint gap measurements[Time frame: 6 months and 1 year after procedure]Changes in MRI with T-2 mapping of the knee cartilageArticular cartilage quality evaluation in T-2 mapping[Time frame: 6 months and 1 year after procedure]

### Statistical analysis

2.5

Results will be expressed as the standard deviations and means. Through utilizing the T-test or Mann-Whitney *U* test, according to normality distribution assessed by Shapiro-Wilk test, the analysis of continuous variables will be carried out. All the statistical analyses will be performed via the software of Statistica. *P*-value less than .05 indicates that there is statistical significance.

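### The arms are compared only by unadjusted two-sample tests although the primary outcomes are changes; adjusting for the baseline value would be more efficient with the same 100 patients

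*Protocol article*

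**What the plan says.** The Outcome measurements section of the protocol article lists two primary outcomes, both worded as changes: "Changes in patients reported outcome measures" (KOOS, whose five subscales are scored separately) and "Changes in the flexibility of the knee joint". Each carries a time frame of 1, 3, 6 and 12 months, and no visit is named as primary. The secondary outcomes are changes on X-ray and on T2-mapping MRI.

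The Statistical analysis section gives one method for all of these. The arms are compared "Through utilizing the T-test or Mann-Whitney" U test, the choice being made "according to normality distribution assessed by Shapiro-Wilk test, the analysis of continuous variables will be carried out". Significance is judged by one rule: a P-"value less than .05 indicates that there is statistical significance". The section names no baseline covariate and no model across visits.

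On size, the Study design section says that "investigators plan to include 100 adults with primary knee osteoarthritis in this study", a number attributed to a power analysis whose inputs the article does not give.

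**The concern.** A change outcome needs a baseline value for every patient, so that value should be available to the analysis at no extra cost. A two-sample test on the change uses it only by subtraction, which fixes its coefficient at 1. When baseline and follow-up correlate imperfectly and have equal spread, that coefficient is too large and baseline noise is added to the comparison. If the test is applied instead to follow-up values, the baseline is not used at all. Either way the arm difference is estimated less precisely than these data allow.

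Precision matters here. The trial has 100 patients, and both arms receive an adipose-derived product, so the difference between arms may be modest (an inference; the article states no expected difference). At stake is the chance of detecting a real difference, and the width of the interval around it.

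This concerns a method the article states, not one it leaves out. A separate analysis plan could improve on it only by replacing it.

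**Working it through.** **The plan's own figure.** The total of 100 cannot be reproduced, because the article gives no effect size, SD, power or dropout allowance. With 50 per arm, two-sided 5% and no dropout (normal approximation), the detectable standardised difference is (1.960 + 0.842) × √(2/50) = 0.56 at 80% power, or 0.65 at 90%. Other combinations also land near 100: a difference of 0.6 SD at 80% power needs 88, or 98 after allowing for 10% dropout. The figure is neither confirmed nor refuted.

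**Inputs**
- From the article: total 100; two randomised groups; significance level 0.05; t-test or Mann-Whitney test.
- Assumed: 1:1 allocation (50 per arm), a two-sided test, complete data, a true difference of 0.5 SD of the raw score, equal baseline and follow-up SDs (set to 1), and a baseline to follow-up correlation r from 0.3 to 0.7.

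**Per-patient variance at one visit, in units of the squared SD**
- follow-up value: 1
- change score: 2(1 − r)
- baseline-adjusted (ANCOVA): 1 − r²
- ratio of ANCOVA to change score: (1 − r²) / [2(1 − r)] = (1 + r)/2, which is below 1 whenever r is below 1

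**Power.** The noncentrality is 0.5 / √(2v/50) = 2.5/√v, where v is the variance above, referred to a noncentral t with 98 degrees of freedom. The one degree of freedom spent on the covariate does not matter.

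| r | v, change | v, ANCOVA | variance saved | power, change | power, ANCOVA |
|---|---|---|---|---|---|
| 0.3 | 1.40 | 0.91 | 35% | 55.3% | 73.7% |
| 0.5 | 1.00 | 0.75 | 25% | 69.7% | 81.6% |
| 0.7 | 0.60 | 0.51 | 15% | 89.2% | 93.4% |

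At r = 0.5, 1/0.75 = 1.33, so the adjustment is worth about 33% more patients.

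**From a common starting point.** Suppose instead that the change-score test has exactly 80% power (normal approximation). ANCOVA at the same visit then has 93.5% (r = 0.3), 89.9% (r = 0.5), 86.0% (r = 0.7) or 84.0% (r = 0.8), a gain of about 4 to 14 percentage points.

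**If the test is applied to follow-up values.** The variance ratio becomes 1 − r²: 0.91, 0.75 and 0.51 at r = 0.3, 0.5 and 0.7. Adjustment again has the smaller variance.

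**Sensitivity to the equal-SD assumption.** Let the follow-up SD be s times the baseline SD. The change-score variance is s² + 1 − 2rs and the ANCOVA variance is s²(1 − r²). Their difference is (1 − rs)², which is never negative, so the direction holds for any s. The size does not. With s = 1.25:
- r = 0.5: 1.3125 against 1.1719, a saving of 11% instead of 25%
- r = 0.7: 0.8125 against 0.7969, a saving of 2% instead of 15%

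**The case against.** The strongest reply is that the stated analysis is not wrong. Under randomisation a two-sample test on changes is valid, and it already uses the baseline by subtraction. That stands. A reader might infer that the comparison is biased through regression to the mean. A chance baseline imbalance can affect the result in one realised sample, but there is no systematic bias over randomisation.

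A reader might also infer that each visit is tested separately on whoever attended, with the earlier scores of dropouts discarded. The article does not say so. A two-sample test takes one value per patient, so four visits imply either separate tests or an unstated summary measure. Missing-data handling may properly sit in a document not shown. No finding on missing data is made here.

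A third tempting reading is that a repeated-measures model would itself add power. Every figure in the power table compares ANCOVA with a change score at one visit. With complete data, the model's contrast at a named visit performs about like ANCOVA at that visit. Its added benefit, use of partial follow-up and validity under missing at random, arises only if visits are missed.

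Finally, the size of the gain rests on assumptions the article does not supply, and the stated plan has a rank-based fallback for non-normal data that a Gaussian model on bounded 0 to 100 scores lacks. Both points stand. The first limits what can be said about size, and the second is met by keeping the stated tests as a sensitivity analysis.

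**Conclusion.** The concern holds as a matter of efficiency. The article fixes an unadjusted test for outcomes defined as changes, and a baseline-adjusted analysis has a smaller variance than a change-score test unless rs = 1, where the two are equal. It also has a smaller variance than a test on follow-up values whenever r is not zero.

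Under the stated assumptions, the gain in power at one visit is about 18 percentage points at r = 0.3, 12 at r = 0.5 and 4 at r = 0.7. Confidence is high in the direction and low in the size: r, the SDs, the difference and the allocation ratio are all assumed, and a follow-up SD larger than the baseline SD can remove most of the gain. The change is worth making because it costs little, but the stated tests would not invalidate the trial.

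**What to change.** - **KOOS subscales and range of motion.** Include the baseline value as a covariate, either by ANCOVA at a prespecified visit or by a mixed model for repeated measures with baseline, arm, visit, arm-by-visit and baseline-by-visit. Report the arm contrast and its 95% CI at that visit. The article names no primary visit, so the investigators must choose one before outcome data are examined by arm.
- **Imaging outcomes.** Use ANCOVA on the baseline image value at each time the outcome is measured. The Outcome measurements section gives these times in two ways: the narrative has before the procedure and 1 year, while the outcome list has 6 months and 1 year. The two should be reconciled first.
- **Sensitivity analysis.** Keep the stated t-test or Mann-Whitney test.

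The cost is revised wording, slightly more analysis work and a model assumption for bounded scores. No patient, visit or measurement is added beyond the baseline value that a change outcome already requires. Adjustment does not settle how the five KOOS subscales and range of motion together support one conclusion.

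### Two equal-rank primary outcomes, one of them scored as five subscales, at four visits with a flat p<.05 and no stated priority: the chance of a false-positive primary result exceeds 5%

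*Protocol article*

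**What the plan says.** In the protocol article, Outcome measurements (2.4) has a heading for primary outcomes with two entries and no ranking between them.

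- **KOOS.** "The KOOS's five patient-relevant dimensions are scored separately": pain, symptoms, activities of daily living, sport and recreation, and quality of life, each put on a 0–100 scale. No total score and no mean of subscales is defined.
- **Knee flexibility.** "Range of motion assessment by goniometer measurements".

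Each entry carries the same schedule: "Time frame: 1, 3, 6, and 12 months after procedure". No visit is singled out.

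Statistical analysis (2.5) covers continuous variables with one approach ("Through utilizing the T-test or Mann-Whitney" U test, chosen after a Shapiro-Wilk test) and one threshold: a P-value "less than .05 indicates that there is statistical significance". It names no longitudinal model, no global test and no order among the outcomes.

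Study design (2.1) describes two randomised groups and 100 patients in total.

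**The concern.** A 5% threshold controls the error of one test. It controls the error of the trial's primary conclusion only if that conclusion rests on one test, or on several tests bound by a rule. Here the primary set holds six scores at four visits, all of the same rank, and the only criterion given is the one for a single test.

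The stated aim is one overall comparison of the clinical effects of enzymatic and mechanical processing, and the Discussion hopes the work will help in choosing between treatment methods. With no endpoint named, a chance difference on one subscale at one visit would satisfy the written criterion for significance and could be presented as a primary result in favour of one method. The reader could not tell whether that subscale and visit had been chosen before or after the data were seen.

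**Working it through.** **Inputs from the article**

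- KOOS scores: 5; range of motion: 1 (Outcome measurements). Counting range of motion once is conservative, because flexion and extension are not distinguished.
- Visits: 4, the same for both outcomes (Outcome measurements).
- Groups: 2, so one between-group comparison per score and visit (Study design).
- Threshold: 0.05 per test (Statistical analysis). Sidedness is not stated; two-sided is assumed.

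The article gives no familywise error rate, so there is no figure of its own to reproduce.

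**Step 1. Count.** (5 + 1) × 4 = 24 possible primary comparisons.

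**Step 2. Independence.** If no true difference exists anywhere, the chance of at least one p<.05 among m independent tests is 1 − 0.95^m.

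- m = 24: 1 − 0.95^24 = 1 − 0.292 = 70.8%
- m = 6 (six scores, one visit): 1 − 0.95^6 = 1 − 0.735 = 26.5%
- m = 2 (two outcomes, one score each, one visit): 1 − 0.95^2 = 9.75%

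**Step 3. Correlated tests.** Subscales of one questionnaire, repeated in the same patients, are positively correlated, so 70.8% is too high for this trial. The article gives no correlations; those below are assumptions. The test statistics were simulated as multivariate normal (400,000 draws, two-sided 5% limit, equal correlation among subscales and among visits).

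| Between subscales | Between visits | KOOS with range of motion | Any p<.05 among 24 | Any p<.05 among 6 at one visit |
|---|---|---|---|---|
| 0.3 | 0.3 | 0.1 | 65% | 24.8% |
| 0.5 | 0.5 | 0.3 | 55% | 21.9% |
| 0.7 | 0.7 | 0.3 | 42% | 18.6% |
| 0.8 | 0.8 | 0.5 | 33% | 15.9% |
| 0.9 | 0.9 | 0.7 | 22% | 12.6% |

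The lowest figure for 24 tests is more than four times the nominal 5% (22 / 5 = 4.4). The lowest for six tests is about two and a half times (12.6 / 5 = 2.5).

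**Step 4. What a plain correction would cost (illustration only).** Bonferroni over 24 tests sets the limit at 0.05 / 24 = 0.0021. Assume 50 patients per arm and 80% power at 0.05, which for a two-sample t-test corresponds to d = 0.57. Power per test then falls to about 38%. The allocation ratio, the power and the effect size are all assumptions; the article states only 100 in total. The figure compares remedies and does not estimate this trial's power.

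**The case against.** The strongest reply is that this is a journal article with a four-sentence statistical section. A multiplicity rule, a testing order and the details of the power calculation are commonly left to a full protocol or analysis plan, which are not shown. That stands as far as it goes: the lack of such a rule is not, taken alone, a fault. The article's remark that the sample size came from a power analysis, without saying for which endpoint, is likewise ordinary condensation and is not part of this point. What remains is what the article does fix: two primary outcomes of equal rank, one with five separate scores, four visits of equal rank, and one unqualified threshold. A later document would have to alter that set, not merely add detail to it.

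A reader might also infer that the plan commits to 24 separate tests, each at 5%. The article does not say so. A time frame says when an outcome is measured and does not promise a test at each visit, and scoring subscales separately describes how the questionnaire works. The count of 24 is the upper limit of a natural reading. The conclusion does not need it, because the six scores at a single visit already give an error rate well above 5%.

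Nor does the article say that any single p<.05 would establish one method as better. That is a use the wording leaves open, not a stated decision rule.

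Finally, 70.8% should not be quoted as this trial's error rate. It requires independence, which is implausible here.

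**Conclusion.** The point holds in this form: the primary set, as written, allows up to 24 unranked between-group comparisons against a flat 5% threshold, so the chance of at least one false-positive primary result is above 5%. The direction held under every correlation tried. The size is not known. It is 71% under independence, about 22% to 65% over the assumed correlations, and about 13% to 26% if testing is confined to the six scores at one visit (the top of that range again being independence).

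These figures assume two-sided tests, no true difference on any score, and correlations that the article does not supply. They do not depend on the sample size. Whether 100 patients are adequate for any particular endpoint cannot be judged from the article and is not claimed either way.

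**What to change.** Before any outcome data are examined, name one KOOS score at one visit as the single primary endpoint, tested at two-sided 5%. The score can be one subscale or a prespecified mean of subscales; change from baseline to 12 months is one suitable choice. The timing matters, because a choice made later cannot be shown to be free of the results.

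Make the other subscales, the other visits and range of motion secondary. Either test them in a fixed order or with Holm, or report them as estimates with 95% confidence intervals and no claim of significance. If range of motion has to stay co-primary, apply Holm to the two tests at the chosen visit.

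The cost is a paragraph in the protocol or analysis plan and a matching update of the registration. The change needs no extra visits and, because the 5% level is not split, does not by itself call for more patients. Since the basis for 100 is not shown, the sponsor should confirm that the existing power calculation fits the endpoint named. The small downside is that results outside that endpoint can no longer be called primary.
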